#### Additional considerations

2.5.5

All participants will be instructed to refrain from engaging in any additional strenuous physical activity involving the lower limbs throughout the intervention period in order to avoid interference with the DOMS recovery process (4). Light daily activities and upper-limb training will be permitted, provided that they do not induce significant muscular fatigue or soreness (4).

### Outcomes

2.6

Table 1 summarizes the assessment moments of the different outcomes. All outcome assessments will be conducted following a standardized temporal sequence throughout the study period (19). Baseline measurements (Day 0) will be performed prior to DOMS induction and before any hypoxic exposure (19).

**Table 1 T1:** Assessment moments of the different outcomes.

Outcome	Assessment moments
Descriptive variables	Day 0
Physical Recovery variables	Days 1, 2, 3, 4, 5
VO_2_max	Days 0 and 5
Hamstring isometric strength	Days 1, 2, 3, 4, 5
Cognitive function (D2, TMT A/B) and stress (DASS-21)	Days 0 and 5
Psychological profile (CPRD)	Day 0
Sprint 30 m	Days 1, 2, 3, 4, 5
Counter Mouvement Jump (CMJ)	Days 1, 2, 3, 4, 5
Squat 1-RM	Days 1, 2, 3, 4, 5
Inflammatory and recovery biomarquers (HIF-1α, PGC-1α, Lactate, Klotho, CK)	Days 1, 2, 3, 4, 5

On Days 1 to 5, all daily assessments of physical recovery, neuromuscular performance, autonomic nervous system activity, and biochemical markers will be performed at the same time of day for each participant (19). Physical performance outcomes will be collected following a standardized warm-up (28).

The study outcomes will be hierarchically structured as follows: hamstring isometric strength will serve as the primary endpoint; additional physical performance, recovery, and biochemical variables will be treated as secondary endpoints; and cognitive and psychological measures will be analyzed on an exploratory basis.

#### Descriptive variables

2.6.1

Age, height, and body weight will be measured to calculate body mass index (BMI, kg/m^2^). Physical activity levels (MET-min/week) will be assessed using the International Physical Activity Questionnaire (IPAQ).

#### Cognitive variables

2.6.2

Given the study's focus on injury prevention, attention and executive function will be assessed using the D2 test and the Trail Making Test (TMT A and B) in Spanish. In these tests, participants are asked to connect numbers and letters in sequential order. Cognition is sensitive to short-term confounding factors such as fatigue induced by the DOMS protocol (18), and we aim to examine whether IH or HH can influence these factors in the short term (29–31). These assessments will be performed on Day 0 (baseline) and Day 5 (post-intervention).

#### Psychological variables

2.6.3

The Depression, Anxiety, and Stress Scale-21 (DASS-21) will be used, which consists of three self-report scales. Each scale contains 7 items, scored from 0 to 3, where 0 means ‘Not at all’ and 3 means ‘Almost always.’ Scores are summed to obtain a total score for each subscale (32). This variable will be assessed on Day 0 (baseline) and Day 5 (post-intervention).

In addition to these tests, the Psychological Characteristics Related to Sport Performance Questionnaire (CPRD) will be used to assess psychological factors relevant to sports performance. The CPRD measures five dimensions: stress control, influence of performance evaluation, motivation, mental skills, and team cohesion. This instrument has demonstrated robust psychometric properties, indicating high internal consistency (33). This variable will be assessed on Day 0 only, with the intention to perform a recovery sub-group secondary analysis based on personality.

#### Physical performance variables

2.6.4

Aerobic capacity (VO_2_ max) will be measured on two occasions: day 0 (before the intervention) and day 5 (at the end of the protocol), using the following procedure: First, a warm-up acsm consisting of 5 min of light jogging or walking at 5–6 km/h with a 1% incline will be performed. Next, a ramp protocol will be conducted, starting at 8 km/h with a 1% incline, with speed increased by 0.3 km/h every 30 s while maintaining the incline, until exhaustion or VO_2_ max criteria are reached (34, 35). The test ends when the participant reaches exhaustion, VO_2_ plateau, or 95% of the age-predicted maximum heart rate according to Tanaka's formula [HRmax = 208−0.7 × age]) (36). Finally, a 5-minute cool-down will be performed, walking at 4 km/h with a 0% incline (37). VO_2_ max will be measured using a SpiroFit metabolic analyzer (SpiroFit/Sendsor GmbH, Grafing, Germany), which enables accurate real-time gas exchange assessment during exercise. The SpiroFit operates by measuring real-time gas exchange (O_2_ and CO_2_) during exercise, allowing for precise determination of VO_2_ max by analyzing oxygen consumption and carbon dioxide production, as highlighted by the articles that demonstrate its validity and reliability comparable to standard laboratory methods (38, 39).

The following tests will be conducted on days 1, 2, 3, 4 and 5:
**30-m sprint speed:** Sprint will be assessed using Witty photocells (Microgate, Bolzano, Italy), which measures velocity over a 30-meter sprint. This test will help evaluate speed and acceleration, key components of athletic performance. A three-minute rest period will be applied between the two attempts to allow full recovery (40).**Countermovement jump (CMJ):** The CMJ is a standing exercise in which the hands are placed on the hips (41). The movement follows the typical eccentric-isometric-concentric sequence of plyometric training, consisting of a downward knee flexion followed by an explosive upward jump. This test will be measured using the MyJump2 app (42), a mobile application for video-based analysis of vertical jump performance used by coaches, athletes, and researchers to assess jump metrics without laboratory equipment. It utilises the smartphone camera to time jump events and derive kinetic and kinematic performance parameters. Each participant will have two attempts, with a three-minute rest period in a standing position between jumps to allow their energy systems to stabilize (43).**Maximum strength (1-RM):** Maximal dynamic strength in the half-squat will be assessed using a Smith machine to prevent anteroposterior oscillations that could interfere with execution velocity measurements (44). A Vitruve VBT encoder (Vitrube, Spain) will be firmly attached to one end of the bar to avoid interfering with the movement. This encoder measures the vertical displacement velocity of the bar (meters per second) and allows 1-RM estimation using the equations by González-Badillo et al. (45). The exercise will be performed with a load equivalent to 80% of each participant's body weight (46). Participants will have two attempts to complete the test, with the best result recorded each time. A three-minute rest interval will be applied between attempts to ensure adequate recovery (47).**Isometric strength:** Maximal voluntary isometric strength will be assessed using an activForce 2 dynamometer. Participants will be asked to generate maximal force in a static position. Since hamstring activity is being recorded, the participant will sit with the knee at a 90-degree angle and the ankle properly positioned on the dynamometer pad, ensuring that the force is transmitted through the hamstrings muscle group while maintaining proper posture and stability. The highest force produced during the trial will be recorded (48).

#### Physical recovery variables

2.6.5

All physical recovery variables will be measured daily on days 1, 2, 3, 4, and 5, before the hypoxia intervention to ensure participants are in a non-fatigued and fully recovered state.

Pressure Pain Threshold (PPT): A mechanical pain threshold analysis will be performed using a Baseline algometer (Wagner instruments, Greenwich, United States). Measurements will be taken on the midpoint of the dominant leg's hamstring muscle belly, defined as the midpoint between the ischial tuberosity and the popliteal crease. Participants will use the Visual Analog Scale (VAS) to rate their hamstring pain on a scale from 0 to 10, where 0 represents no pain and 10 represents the worst possible pain. To ensure reproducibility, three measurements will be taken at each site with a 30-second interval between trials, and the mean value will be used for analysis. The same examiner, trained in algometry procedures, will perform all measurements (49, 50).

Muscle oxygen saturation (SmO_2_) will be monitored in real time with a Moxy Monitor (Fortiori Design LLC, Hutchinson, MN, USA) placed on the hamstrings muscle group, while the participant is performing an effort during the 30 m sprint (51).

Autonomic nervous system (ANS) activity will be assessed using heart rate variability (HRV) measured with a Polar H10 chest strap (Polar Electro Oy, Kempele, Finland). The strap will be positioned around the participant's thorax, just below the sternum and in contact with the skin at the level of the xiphoid process, ensuring firm placement for optimal signal acquisition. Measurements will be taken in a seated, rested position for 5 min, and participants will be instructed to avoid speaking or moving during the recording. To ensure reproducibility, each measurement will be performed at the same time of day, by the same trained investigator, and the mean of three consecutive recordings will be used for analysis. Polar H10 chest straps have been shown to provide high validity and reliability for HRV measurement compared to standard ECG systems in both laboratory and field settings (52). Beyond standard HRV metrics, advanced ANS indices will be extracted using validated signal-processing algorithms to characterize sympathetic and parasympathetic modulation more comprehensively. Variables such as the Stress Index, parasympathetic activation scores, and overall autonomic balance will be collected each day before the hypoxia intervention (53). These indicators will allow assessment of physiological stress, recovery status, and autonomic regulation throughout the protocol, offering an additional layer of interpretation regarding the systemic impact of DOMS combined with intermittent hypoxia (53).

Active knee extension range of motion: Participants will be positioned supine with the hip joint maintained at 90° of flexion. They will be then instructed to voluntarily extend the knee as far as possible while keeping the hip flexion locked at 90°. In this phase, hamstring flexibility will be assessed by measuring the knee extension range of motion with the App *Goniometer Pro* (Digiflex Labs/Avvi LLC, iOS) (54).

Body composition will be assessed using the BIODY XPERT ZM3 (Aminogram SAS/eBIODY, La Ciotat, France) device, which provides multi-frequency bioelectrical impedance measurements, including the phase angle (55). Measurements will be performed under standardized conditions each day before the hypoxia intervention to ensure consistency. The phase angle, derived from the relationship between reactance and resistance, reflects cellular integrity and membrane functionality. Although it does not directly quantify oxidative stress, reductions in phase angle have been associated with increased cellular stress, altered membrane permeability, and elevated inflammatory or oxidative processes (56). Thus, in this study, the phase angle will be used as an indirect biomarker of cellular stress potentially influenced by intermittent hypoxia and DOMS (56, 57). Daily monitoring will allow evaluation of acute fluctuations in cell health and their relationship with performance and recovery markers.

#### Biochemical markers

2.6.6

The selection of biochemical markers in this study was designed to capture complementary aspects of the physiological response to exercise-induced muscle damage and hypoxic-based recovery interventions, rather than to provide redundant information (13, 58). Specifically, the chosen biomarkers reflect molecular signaling, metabolic stress, muscle damage, and systemic recovery processes relevant to DOMS (4).

Inflammatory markers: This procedure will be repeated on days 1, 2, 3, 4, 5. On day 1, the first measure will be taken prior to any physical activity, and the second will be taken right before the hypoxic intervention. On days 2, 3, 4, 5 there will only be one measurement prior to the hypoxic intervention. This sampling schedule is designed to capture the systemic inflammatory response that emerges approximately 24 h after exercise-induced muscle damage, rather than the acute changes that occur immediately post-exercise, which are more transient and variable. Measuring prior to the hypoxic intervention on subsequent days allows assessment of the 24-h post-stimulus inflammatory status, reflecting the cumulative effects of prior activity and recovery processes (59). Various biomarkers related to inflammation, muscle damage, and stress response will be assessed, including HIF-1α, PGC-1α, and Klotho protein.

To assess inflammatory markers, venous blood samples (∼5 mL per sample) will be collected by a trained nurse via venipuncture using EDTA-containing tubes to prevent coagulation. The venipuncture procedure will be carried out as follows: the participant will sit in a chair, and the nurse will locate an accessible vein in the arm. Once the vein is identified, the area will be disinfected, and a sterile single-use needle will be inserted to draw the blood sample in vacutainer tubes. Prior to sampling, the site will be cleaned with an alcohol swab, and standard aseptic procedures will be followed to minimize contamination and hemolysis. After collection, samples will be immediately placed on ice and processed within 1 h, including centrifugation to separate serum or plasma, and stored at −80 °C until analysis. Subsequently, plasma will be separated by centrifugation at 2000–2500×*g* for 15 min at 4 °C and rapidly stored at –80 °C to preserve biomarker integrity. Concentrations of specific biomarkers will be quantified using enzyme-linked immunosorbent assay (ELISA) kits (R&D Systems, Minneapolis, MN, USA) according to the manufacturer's protocol. For HIF-1α, in addition to ELISA, Western Blot will be employed as a complementary technique to confirm protein expression and better evaluate its regulation in response to hypoxia (60).

HIF-1α is a key transcription factor in the hypoxic response. Its activation regulates the expression of genes involved in cellular adaptation to low-oxygen conditions, such as energy metabolism and angiogenesis. HIF-1α was selected as a primary molecular marker of hypoxic signaling and cellular adaptation to reduced oxygen availability (13).

PGC-1α is a transcriptional coactivator involved in mitochondrial biogenesis and exercise adaptation. Its expression increases following physical activity, promoting muscular endurance and metabolic efficiency. Assessing its levels will provide information on cellular adaptation capacity and recovery potential (58). PGC-1α will be assessed using complementary molecular techniques. Quantitative PCR will be employed to measure mRNA expression levels, while Western blot analysis will be conducted to confirm protein abundance. For qPCR, total RNA will be extracted from peripheral blood mononuclear cells obtained from venous blood samples collected from participants. RNA isolation will be performed using commercially available RNA extraction kits following the manufacturer's general instructions. This dual approach ensures comprehensive evaluation of both transcriptional and translational regulation of PGC-1α.

Klotho is a protein associated with healthy aging and cellular protection against oxidative stress, inflammation, and tissue damage. Its expression has been linked to improved muscle regeneration, mitochondrial function, and insulin sensitivity, key aspects during post-exercise recovery. Following intermittent hypoxia or hypoxia-hyperoxia interventions, Klotho levels are expected to increase as part of the body's adaptive response. Analyzing this protein will allow evaluation of the systemic impact of recovery strategies on redox balance, cellular longevity, and metabolic performance (61).

Additionally, CK and blood lactate were selected as established markers of muscle damage and metabolic stress, respectively, allowing confirmation of exercise-induced muscle stress and characterization of recovery dynamics across the intervention period (4, 62). Blood lactate and creatine kinase (CK) levels will be measured using capillary blood samples obtained via safety lancets from the fingertip. All samples will be collected following standard aseptic procedures to ensure accuracy and minimize discomfort.

Blood lactate concentration will be measured using a portable analyzer (Lactate Scout Sport, EKF Diagnostics, Cardiff, UK). Lactate levels are expected to be elevated after demanding exercises, particularly those involving eccentric contractions, and will be used as an important marker to detect metabolic stress, fatigue, and to monitor physiological adaptation following intense physical activity (62, 63).

CK levels will be measured as a key biomarker to assess muscle damage and recovery following intense physical activity involving eccentric contractions. For the analysis, the SimplexTAS 101 point-of-care clinical chemistry and immunoassay analyzer (TASCOM Co., Ltd., Anyang-si, Gyeonggi-do, Republic of Korea) will be used.

### Statistical analysis

2.7

All statistical analyses will be performed using IBM SPSS Statistics version 29 (IBM Corp., Armonk, NY, USA). The primary confirmatory analysis will focus on hamstring isometric strength. The normality of the variables will be assessed using the Shapiro–Wilk test. Descriptive analysis will be performed using the mean ± standard deviation for normally distributed data, or the median and interquartile range for data not following a normal distribution.

The principal analysis will evaluate the Group × Time interaction using repeated-measures ANOVA, as this term reflects the differential effect of the intervention over time between groups. When significant interaction or main effects are observed, Bonferroni-adjusted *post hoc* comparisons will be conducted. Effect size will be evaluated using partial eta squared (*η*^2^*p*).

Analyses will be conducted according to the intention-to-treat principle, including all randomized participants in the groups to which they were allocated. Missing data will be handled using multiple imputation procedures under the missing-at-random assumption prior to conducting the repeated-measures ANOVA.

Secondary outcomes will be analyzed using the same analytical approach. Where multiple comparisons across secondary endpoints are conducted, Bonferroni correction will be applied within each family of related outcomes.

Cognitive and psychological variables will be analyzed on an exploratory basis. Correlation analyses (Pearson or Spearman) and multiple linear regression models will be performed to explore potential associations and predictors of cognitive improvement or functional recovery. The level of statistical significance will be set at *p* < 0.05.

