The novelty of this research lies in exploring IH and HH exposure as comprehensive methods for muscle recovery, as they may influence not only muscle repair but also cognitive recovery and mental performance, which are often impaired by DOMS (17). Beyond localized muscle soreness, DOMS induces systemic and peripheral inflammatory responses and sustained nociceptive signaling that engage central somatosensory and motor processing networks, potentially influencing cognitive and psychomotor performance during recovery from intense exercise (18). The purpose of this study is to determine whether HH and IH can be effective techniques for DOMS recovery. Our hypothesis is that both HH and IH will accelerate recovery from DOMS. Additionally, given the alternating hyperoxic stimulus and the potentially amplified cellular signaling associated with hypoxia–hyperoxia protocols, we hypothesize that hypoxia–hyperoxia may induce greater improvements in recovery-related outcomes than intermittent hypoxia alone (17).

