### Sample size

2.4

The primary outcome of this trial is hamstring isometric strength. The required sample size was determined *a priori* using G*Power 3.1 considering a repeated measures of variance (ANOVA) design. In the absence of prior data to inform the expected magnitude of change, a conventional medium effect size (*f* = 0.25), as defined by Cohen, was assumed. With a significance level of *α* = 0.05, a statistical power of 0.80 (*β* = 0.20), and six time points, the analysis indicated that 36 participants would be required to detect statistically significant differences between groups. To account for potential dropouts and non-compliance, an additional 20% contingency was applied, increasing the total sample size to 45 participants (15 per group).

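### The principal test of hamstring strength is an omnibus Group × Time interaction with the pre-treatment value as a level of time, so a significant result does not by itself support the three arm comparisons the trial hypothesises

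*Protocol article*

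**What the plan says.** Section 2.4: "The primary outcome of this trial is hamstring isometric strength". Section 2.7 fixes its analysis: "The principal analysis will evaluate the Group × Time interaction using repeated-measures ANOVA". No baseline covariate is named. The follow-up rule is: "When significant interaction or main effects are observed, Bonferroni-adjusted *post hoc* comparisons will be conducted". It does not say which pairs of arms or which days are compared.

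The Introduction states the aim as arm comparisons: "Our hypothesis is that both HH and IH will accelerate recovery from DOMS". It adds that HH may do better than IH alone.

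On timing, Table 1 and section 2.6.4 put hamstring strength on Days 1 to 5. Section 2.5.2 places baseline measurements on Day 1 before the induction exercise, and section 2.5 starts the breathing sessions on Day 1 after it. Section 2.4 counts six time points rather than five.

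**The concern.** The first strength value precedes treatment, so randomisation makes the arms equal on it in expectation and it can carry no treatment effect. In a Group × Time ANOVA it nevertheless enters as one more response. Its natural use is as a covariate that explains part of the between-person variation in later strength.

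The omnibus F also answers a broader question than the trial asks. It rejects for any difference in profile among three arms: one active arm differing, both differing, or the two active arms differing only from each other, in either direction. If the principal result is significant, the reader still does not know whether IH beat placebo, HH beat placebo, or HH beat IH. Those claims would then rest on follow-up comparisons whose number and days are open.

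**Working it through.** **Inputs.** From the document: three arms at 1:1:1; strength on five days, the first before treatment; 36 participants, raised to 45 (15 per arm). The document gives no SD, correlation or effect profile. I assume unit SD, equal correlation ρ between days (0.5, 0.7, 0.8), and Days 2–5 as the post-treatment days. That last assumption holds if strength is tested before each day's session, as section 2.6.5 states for the recovery variables.

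**The plan's own figure.** Section 2.4 assumes "a conventional medium effect size (*f* = 0.25), as defined by Cohen, was assumed". For an interaction with sphericity, λ = f²·N·m/(1−ρ), with df 10 and 5(N−3).
- ρ = 0.5, N = 24: λ = 0.0625×24×6/0.5 = 18, power 0.81.
- ρ = 0.5, N = 36: λ = 0.0625×36×6/0.5 = 27, power 0.96.
- 36 is the smallest balanced total for 0.80 only if ρ is about 0.22–0.28, which is not stated.
- Dropout step: 36/0.8 = 45, correct.

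Read as an interaction test, this calculation sizes the omnibus F and gives no power for any arm contrast.

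**Degrees of freedom.** (3−1)(5−1) = 8 with five points; (3−1)(6−1) = 10 with six.

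**Baseline as response or covariate.** Take an effect of constant size on Days 2–5. The interaction's information on it equals that of the Day 2–5 mean minus baseline. Per-person variances:
- change from baseline: (1+3ρ)/4 + 1 − 2ρ
- baseline-adjusted: (1+3ρ)/4 − ρ²
- share of information kept = adjusted/change = (1+4ρ)/5

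| ρ | Change | Adjusted | Share kept |
|---|---|---|---|
| 0.5 | 0.625 | 0.375 | 60% |
| 0.7 | 0.375 | 0.285 | 76% |
| 0.8 | 0.250 | 0.210 | 84% |

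For one arm contrast on the Day 2–5 mean at 0.05/3, with 15 per arm, 0.6 SD and ρ = 0.7, the standard errors are √(2×0.375/15) = 0.224 and √(2×0.285/15) = 0.195. The ratios of effect to standard error are 2.68 and 3.08. Simulated power is about 0.56–0.58 for change from baseline and 0.67–0.72 with adjustment. Adjustment was also better in every building or fading profile tried.

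For outcomes measured only on Days 0 and 5 the variances are 2(1−ρ) and 1−ρ². The share kept is (1+ρ)/2: 75%, 85% and 90%.

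**The post hoc step.** Three averaged contrasts would each be tested at 0.05/3 = 0.0167; three pairs on each of five days at 0.05/15 = 0.0033. Section 2.7 does not choose. Section 2.5.2 counts a fall in strength or performance as a sign of successful induction, so a Time main effect is expected even if treatment does nothing.

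**Interaction or average contrast?** Simulation: 15 per arm, five points, both active arms equal, ρ = 0.7, effects in SD on Days 2, 3, 4 and 5. Ranges cover separate runs.

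| Profile | Interaction (8 df) | ANCOVA on Day 2–5 mean (2 df) |
|---|---|---|
| Sustained: 0.6 on all four days | 0.52–0.55 | 0.85–0.87 |
| Building: 0, 0.2, 0.4, 0.6 | 0.51–0.53 | 0.30–0.31 |
| Building: 0.2, 0.4, 0.6, 0.8 | about 0.71 | about 0.71 |
| Peak and fade: 0.4, 0.8, 0.4, 0 | 0.76–0.78 | 0.51–0.52 |

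The ordering depends on the shape of the effect.

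**The case against.** The strongest reply is that faster recovery means curves that diverge, or diverge and then meet again. That is a change in profile, which is what the interaction tests. The table bears this out: for several building or fading effects the omnibus test beats the averaged contrast by 20 points or more. A reader might infer that the interaction generally wastes power. The document fixes no profile or correlation, so that inference is not supported.

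A reader might also infer that the hypotheses go untested. They do not: the interaction is a valid test of differential change, and Bonferroni comparisons follow it. What stands is narrower. The principal test alone does not establish any of the three claims, and the follow-up is not tied to them. The gate could be read more kindly, with a Time effect opening only comparisons between days, but the sentence does not say so. A separate analysis plan may name the pairs and days; the choice of principal test and the omission of baseline adjustment from it are made here.

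Two further inferences should be resisted. One is that type I error is inflated through lack of sphericity; section 2.7 does not rule out a correction, and under compound symmetry the simulated null rate was 0.046. The other is that imputing before the ANOVA is a defect ("Missing data will be handled using multiple imputation procedures under the missing-at-random assumption prior to conducting the repeated-measures ANOVA"). How the F tests are corrected and pooled is ordinary analysis-plan detail.

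**Conclusion.** The point holds in limited form and merits a change before analysis. The principal test is valid, but a significant result would not by itself show that IH or HH improves recovery over placebo, or that HH is better than IH. This does not depend on any assumed number.

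Leaving baseline out as a covariate costs about 40%, 24% or 16% of the information on a constant effect at ρ = 0.5, 0.7 or 0.8, under equal variances and equal correlations. Adjustment recovers this from data already planned.

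Replacing the interaction with a Day 2–5 average is a trade-off. The gain from about 0.52 to 0.85 applies to a sustained effect; the losses, from about 0.53 to 0.30 and from 0.76 to 0.52, arise for effects spread over several days.

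**What to change.** Reword section 2.7 as follows.

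- Analyse strength on Days 2–5 in a mixed model with arm, day, arm × day, Day 1 pre-induction strength and baseline × day. Missing days are then handled under the missing-at-random assumption already made.
- Name IH vs placebo, HH vs placebo and HH vs IH as the confirmatory contrasts over stated post-treatment days, Holm or Bonferroni adjusted, and do not gate them on a Time main effect.
- Choose the days or summary to match the expected recovery shape, give the reason, and keep arm × day as a supportive test.
- For outcomes measured only on Days 0 and 5, use ANCOVA with the Day 0 value as covariate.

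State the assumed correlation in section 2.4 and give power for the contrasts. The 2-df figures above are not that power. For a sustained 0.6 SD effect with 15 per arm, one Bonferroni contrast on the Day 2–5 mean has about 0.55, 0.72 and 0.85 at ρ = 0.5, 0.7 and 0.8. Both active-versus-placebo contrasts together have about 0.40, 0.57 and 0.76.

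The change needs no new data or visits, and SPSS can fit the model. Its cost is the rewording and a reasoned choice of days. An average over Days 2–5 is less sensitive to effects that build up or fade over several days, not only to an effect on a single day.

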#### Day 1: DOMS induction

2.5.2

Before the DOMS induction, baseline measurements in normobaric conditions will be performed.

The exercise protocol to induce hamstring DOMS through eccentric contractions will include the following exercises: Nordic Hamstring Exercise (5 sets × 5 reps, rest = 90 s); Bilateral Leg Curl (5 sets × 8 reps, 80% 1RM, rest = 90 s); Romanian Deadlift (5 sets × 8 maximal reps, rest = 90 s), and Bilateral Leg Curl eccentric phase only (5 sets × 8 reps, 130% 1RM, rest = 90 s). This protocol was designed based on previous studies (21).

The selected protocol emphasizes high-volume and high-intensity eccentric contractions of the hamstring muscle group, which have consistently been shown to induce exercise-induced muscle damage and delayed onset muscle soreness in physically active individuals (21). Similar eccentric-based protocols have demonstrated reproducible increases in muscle soreness, reductions in strength, and alterations in functional performance within 24–72 h post-exercise (4, 21).

To confirm the success of DOMS induction, subjective measures of muscle soreness and objective neuromuscular performance will be assessed at baseline and daily throughout the intervention period (4). A clinically significant increase in perceived muscle soreness, along with concomitant reductions in strength or performance, will be considered indicative of successful DOMS induction. Creatine kinase (CK), an indicator of muscle damage, will also be assessed to ensure that DOMS has been successfully induced (4).

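### Between-arm comparisons of hamstring strength are not tied to the Group × Time interaction, because a significant main effect can also release them

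*Protocol article*

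**What the plan says.** Section 2.7 (Statistical analysis) names hamstring isometric strength as the outcome of the primary confirmatory analysis. It makes the Group × Time interaction from a repeated-measures ANOVA the principal analysis, because that term carries the differential effect of treatment. The rule for follow-up tests is: "When significant interaction or main effects are observed, Bonferroni-adjusted" post hoc comparisons are made. On the error level: "The level of statistical significance will be set at *p* < 0.05".

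The section does not say which comparisons follow which effect, or how many comparisons the Bonferroni adjustment covers for the primary outcome. Secondary outcomes use the same approach, with Bonferroni within families of related outcomes.

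Two other places bear on this:
- Section 2.5.2 (Day 1: DOMS induction) says that eccentric protocols like the one used "have demonstrated reproducible increases in muscle soreness, reductions in strength, and alterations in functional performance within 24–72 h post-exercise", and it places the baseline measurements before induction.
- Section 2.6.4 and Table 1 schedule strength on Days 1 to 5: "The following tests will be conducted on days 1, 2, 3, 4 and 5".

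**The concern.** The interaction is named as the term that measures the treatment effect, but the next sentence lets other terms open the comparisons through which arms are declared different.

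These comparisons matter. The Introduction's hypotheses are about particular arms: each active arm should speed recovery, and hypoxia–hyperoxia should do better than intermittent hypoxia. A significant three-arm interaction does not say which arm differs, so the trial's claims will rest on the post hoc comparisons.

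The two main effects raise different problems:
- **Group.** This effect averages over all days, including the pre-treatment Day 1 value. It is a second test of arm differences at 5%, beside the interaction.
- **Time.** The induction protocol is meant to reduce strength in every arm, so this effect is close to certain. If it is read as opening arm comparisons, the condition restricts nothing.

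An arm difference on the primary outcome could then be reported although the principal test is not significant. If the reading is chosen after the data are seen, that choice itself affects the conclusion.

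**Working it through.** **Inputs from the documents.** Three arms at 1:1:1; 45 participants, 15 per group (section 2.4); level 0.05 (section 2.7); strength on five days (section 2.6.4), against six time points in section 2.4, so both were run.

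**Assumed, because not stated.** Compound symmetry, correlation 0.3–0.9 between repeated measures, no missing data, no arm difference on any day, and the same time course in all arms with a peak drop of 1.2 SD. Each setting used 40,000 simulated trials. A repeat with a 1 SD drop and 20,000 trials per setting gave closely similar results.

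**The plan's own figures.** 36/(1 − 0.20) = 45, so the inflated sample size reproduces. The 36 itself cannot be confirmed or refuted, because the correlation and the sphericity correction are not given; nothing below depends on it. The 5% level of the principal test also reproduces: the interaction F test (8 and 168 df with five time points, 10 and 210 with six) was significant in 4.7–5.0% of null trials.

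**Step 1: the time effect.** It was significant in essentially every null trial (at least 99.9%).

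**Step 2: each effect followed only by its own contrasts.** The group effect remains as a second route.
- Two independent 5% tests: 1 − 0.95² = 9.75%.
- Simulated, interaction or group effect significant: 9.4–9.8% (repeat: 9.2–10.2%).
- Simulated, interaction significant or a Bonferroni-adjusted marginal arm contrast significant: 8.8–9.1% (repeat: 8.5–9.4%).

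**Step 3: the time effect also read as opening arm-by-day comparisons.** There are 3 pairs per day, so 3 × 5 = 15 or 3 × 6 = 18 in all. The per-test level is 0.05/3 = 0.0167 if Bonferroni covers one day, and 0.05/15 = 0.0033 or 0.05/18 = 0.0028 if it covers all pairs and days.

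| Gate | Bonferroni family | Null trials with at least one false arm difference |
|---|---|---|
| Open | 3 pairs per day, five time points | 9.3–18.4% (16.8% at correlation 0.5) |
| Open | 3 pairs per day, six time points | 10.0–21.4% (19.1% at correlation 0.5); repeat up to 22% |
| Open | all 15 or 18 pairs | 2.1–4.3% |
| Interaction only | 3 pairs per day | 0.7–3.2% |

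Leaving out the baseline day changes the open-gate, per-day range only to 8.4–18.5%.

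**Step 4: either route counted.** If an arm effect is claimed on a significant interaction or on any comparison released by the open gate, the null error is 6.9–8.4% with Bonferroni over all pairs and days, and 13.6–23.0% with Bonferroni per day.

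**The case against.** The strongest reply is that the confirmatory test is named, is a single test and holds its level. What follows it is called post hoc and is adjusted. A reader might infer from the wording that the confirmatory analysis as a whole does not hold 5%. The document does not support that: the interaction test keeps 4.7–5.0%, and follow-up tests cannot change it.

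A reader might also infer that the built-in time effect automatically releases arm comparisons, and that error is therefore several times nominal. The text does not say so. The usual reading is that time is followed by day-against-day contrasts, group by marginal arm contrasts, and interaction by arm-by-day contrasts. Nor does section 2.7 say that Bonferroni covers only three pairs per day. The 9–22% range depends on both assumptions; with the wider family, the comparisons stay at 2–4% without any gate.

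It is also tempting to say that chance baseline imbalance inflates the group test. It does not: under randomisation it is already inside that test's 5%. Including the pre-treatment value dilutes a real effect but does not add false positives.

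Finally, an article may leave the exact post hoc family to an analysis plan, so its absence alone is no fault.

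All of this stands. It does not answer the narrower point. The release on main effects is a stated rule. Even on the usual reading it adds the group effect as a second route to an arm claim, at about 9% in total.

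**Conclusion.** The point holds as a defect in the rule for follow-up comparisons, not in the principal test. Section 2.7 does not tie between-arm comparisons of the primary outcome to the interaction. On the narrow reading, the null chance of an arm claim through the interaction or the group effect is about 9–10%, against a nominal 5%. On the wide reading, the chance of a false arm difference runs from 2–4% to 9–22%, depending only on the Bonferroni family. With the interaction as the only gate, even the per-day family gives about 1–3%.

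The figures rest on 15 per arm, compound symmetry and correlations of 0.3–0.9, and cover only the case of no arm difference at all. If one arm truly differs, the interaction gate may open legitimately and the Bonferroni family alone protects the remaining pairs. That is why both parts of the rule need fixing.

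**What to change.** In section 2.7, before group codes are broken:
- remove main effects as a trigger for between-arm comparisons of hamstring isometric strength, so that these follow only a significant Group × Time interaction;
- state that Bonferroni covers all arm-by-day pairs tested;
- describe the group and time main effects as descriptive;
- apply the same gate to secondary outcomes, alongside the correction within outcome families already planned.

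This takes one or two sentences and changes neither design nor sample size. The downside is fewer day-specific significant results to report. A new confirmatory family, such as contrasts averaged over the recovery days or adjusted for baseline, is not needed for this point and would change what the trial estimates.
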